### Data analysis

We intend to use an optimal design in which treatment arms are allocated following a multi-site cluster randomization procedure [43]. A preliminary analysis will compare baseline characteristics between intervention and control condition sites, as well as sites enrolled in the project and eligible sites that chose to not participate. Chi-square tests and linear models will be used to formally test for statistically significant baseline differences between the arms. Descriptive statistics and plots will be used to summarize the distribution of each of the analytic variables collected at each time point for each arm. The organizational site is the unit of analysis.

For the primary outcome analysis, mixed-effects models (random effects due to organization and fixed effects due to study arm and time) will be used for data analysis of the monthly number of assigned and open buprenorphine slots per organization, estimated extended-release naltrexone capacity, buprenorphine use, and extended-release naltrexone use. A number of organizational characteristics found by Knudsen et al. [45] to affect the presence of physicians in addiction treatment setting, including facility type, services offered, and organizational size, will be included in the models as covariates to properly and efficiently estimate the effect of PRB. We will examine the PRB effect at each time point using cross-sectional multilevel models and will also implement growth curve models across time that include the PRB effect, time, and PRB*time, as well as time-varying covariates and organizational characteristics. The available and open buprenorphine slots, extended-release naltrexone capacity, buprenorphine use, and extended-release naltrexone use will be measured repeatedly for the same subjects, and it is expected that these values will be correlated over time. Therefore, instead of assuming an independence (i.e., zero correlation) or a compound symmetry covariance structure (i.e., a constant correlation regardless of the proximity of measurement time points), we will allow errors to be auto-correlated or Toeplitz structured, denoted as AR(p) or TOEP(p), in the growth curve models. This can be done by allowing additional parameters in the mixed-effects model error structures that represent the correlation between the adjacent measures of outcomes, and is reduced as the measures become further apart [46]. For the meditational analysis, we will examine the mediating effects of resources dedicated to physician satisfaction and PRB implementation fidelity through a causal mediational analysis. Each of the factors will be aggregated at the organizational site level and measured using mixed-effects models. Through a mediation analysis [47, 48], we can estimate the direct (buprenorphine slots, extended-release naltrexone, buprenorphine use, and extended-release naltrexone use with and without PRB) and indirect effects (resources dedicated to prescriber recruitment, staff prescriber satisfaction, and PRB implementation fidelity) of the PRB on the outcome measures. Using the R package “mediation,” we will estimate the causal mediation effects, examine moderated mediation effects, and conduct sensitivity analysis at each time point as well as across time [49].

The qualitative analysis will include deductive and inductive components. The Burke-Litwin model will provide the domains for a directed content analysis [50]. An inductive approach based on grounded theory and dimensional analysis [51–54] will be used to identify and explore additional contextual and processual factors that affect PRB implementation. Both directed and inductive analyses will include within-site and cross-site comparisons. Qualitative analysis will begin with the first interview and will continue in tandem with data collection, allowing the investigators to use later interviews to delve into factors identified in early interviews. Together, these approaches will produce a thorough description of PRB implementation that will be combined with the quantitative results to deepen our understanding of how the PRB works, promoting insights that can be applied to future dissemination of the PRB, and to discover strategies beyond the PRB that contributed to prescriber recruitment.

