### Randomization and consent procedures

The first stage of the block randomization within each state is to develop sampling matched organizations from those that agreed to participate, based on their current use of PRB practices (i.e., number of PRB practices being used 0–7) and whether they were currently prescribing buprenorphine (i.e., yes or no). As a result, 11–13 matched pairs are identified per state. For Ohio and Wisconsin, one matched pair will have two intervention sites to one control site, due to the overall uneven number (*n* = 23). A random number generator is utilized to assign organizations within each pair into one of the two study conditions. Following randomization, study staff will provide University of Wisconsin Institutional Review Board approved study information sheets to staff participants. No visible concealment will be applied. Blinding of participants and researchers is considered logistically infeasible.

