### Timeline

During project months 1 to 18, the study team will design the PRB intervention, complete IRB approval, and identify and recruit treatment organizations. In months 14 to 18, the study team will collect baseline data on number of assigned and open buprenorphine slots and extended-release naltrexone capacity. In months 15 to 42, the study team will implement the study arm interventions and collect outcome data on the 24-month staggered start intervention. During months 37 to 52, the study team will collect quantitative data on the sustainability of the changes. Data analysis, publication development, and dissemination of findings will occur at several points, but primarily during months 53 to 60.

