### Sample size

In determining sample size, we fit a linear mixed-effects model to the monthly results for assigned and available buprenorphine slots to estimate the “PRB with NIATx organizational change model” effect. The power of the study design was determined by the anticipated standardized effect size based on the effects experienced in the PRB pilot study. The PRB pilot study, which included 8 organizations, found that PRB increased physician recruitment by 43.4–100%, which can be transformed into Cohen’s *d* = .394 on average [41]. Intraclass correlation (ICC) among sites affects the power of cluster randomized trials [42]. The estimate of ICC was around 0.10. We will have recruited 35 treatment sites and 35 comparison sites. Based on our previous and current projects with similar participants, we expect about 15% attrition by the end of the data collection, so we used a more conservative 20% attrition rate for our power calculations. With 28 organizations in each condition with an average of 150 buprenorphine slots in each organization, the study will achieve a power of .93 (*d* = .30) or higher (*d* > .30) with a type I error rate of 0.05. Power calculation for the cluster RCT was performed using Optimal Design Software [43].

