### Data collection and measures

The primary outcome variables are the monthly number of (a) assigned and (b) open buprenorphine slots as well as (c) extended-release naltrexone capacity and (d) administrations over the past month. *Assigned slots* are defined as the number buprenorphine slots all prescribers affiliated with the organization have dedicated to the organization. For the buprenorphine data, on the first working Monday of the month, each organization will count the numbers of assigned and open buprenorphine slots. For extended-release naltrexone data, the number of extended-release naltrexone administrations for the previous month will be counted. These data will be collected during the 4-month planning phase, the 20-month rollout phase, and the 10-month sustainment phase, for a total of 34 months.

For the mediational analysis, at organizational baseline, mid-intervention, and the end of the intervention phases, the PRB change leader (or primary contact) will complete the organizational surveys for the PRB implementation fidelity. In addition, any physician affiliated with the organization (by employment or contract) will complete the Physician Worklife Survey [21].

The qualitative portion of the study will support the research questions by exploring facilitators and barriers to successful prescriber recruitment, as well as the process of PRB implementation within organizations and fidelity to PRB implementation sequence. Sampling for the qualitative component will promote integration of qualitative and quantitative approaches by drawing upon findings from the quantitative assessments. Semi-structured interviews will be conducted with up to 15 organizations in the intervention arm that have had success at implementing the PRB (at least 5 of the 7 practices from the PRB fidelity scale) and up to 15 organizations that have implemented fewer than 3 PRB practices at the end of the first year or mid-point of the intervention. In this longitudinal design, selected organizations will be interviewed at end of the mid-point and at the end of the intervention period to allow for more in-depth exploration of what occurred within these organizations over time.

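### The primary models omit the factors that restricted the randomization (state, matched set) and the pre-start count, which costs precision in comparisons of level

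*Protocol article*

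**What the plan says.** **Allocation.** Under Randomization and consent procedures, randomization is blocked within each state. Sites are first matched "based on their current use of PRB practices (i.e., number of PRB practices being used 0–7) and whether they were currently prescribing buprenorphine", and a random number generator then assigns arms within each pair. Ohio and Wisconsin, with 23 sites each, each have one set with two intervention sites and one control. The Data analysis section repeats that "treatment arms are allocated following a multi-site cluster randomization procedure".

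**Model.** Data analysis states that "mixed-effects models (random effects due to organization and fixed effects due to study arm and time) will be used for data analysis" of the monthly outcomes. The next sentence adds organizational characteristics taken from a cited study, including facility type, services offered and organizational size, and gives proper and efficient estimation of the PRB effect as the reason. Two analyses follow:
- cross-sectional multilevel models at each time point;
- growth curves with PRB, time, their interaction, time-varying covariates and organizational characteristics, with AR or Toeplitz errors.

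**Baseline.** According to the Timeline, in months 14 to 18 "the study team will collect baseline data on number of assigned and open buprenorphine slots and extended-release naltrexone capacity". The outcome series itself starts later: "These data will be collected during the 4-month planning phase, the 20-month rollout phase, and the 10-month sustainment phase". Data analysis uses baseline data to compare the arms, and enrolled with non-participating sites. It does not use them as a term in the outcome model.

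**The concern.** Matching and blocking make the arms more alike than simple randomization would, so the true sampling variance of the arm difference is smaller. A model without those factors leaves their variance in the between-site residual and reports a standard error that is too large. The test then rejects less often than its nominal level, the intervals are too wide, and the gain from matching is lost. The random organization effect does not repair this: it describes repeated months within a site, not the likeness of two sites in one matched set.

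The pre-start count raises a separate point. Sites that already hold many slots are likely to hold many later, so the baseline value should explain much of the between-site spread. With at most 70 sites, and 56 in the power calculation, precision matters. Facility type, services and size may absorb some of this variance, but none of them is the baseline outcome or a randomization factor.

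**Working it through.** **1. The plan's own figure.** Inputs from Sample size: 28 sites per arm (J = 56), n = 150 slots per site, "The estimate of ICC was around 0.10", d = 0.30, "with a type I error rate of 0.05". The noncentrality is

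d·√J/2 ÷ √(ICC + (1 − ICC)/n) = 0.30 × 7.483/2 ÷ √(0.10 + 0.90/150) = 1.1225 ÷ 0.3256 = 3.448.

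Two-sided power is 0.923 (noncentral F, 54 df) or 0.932 (normal approximation). The article states "a power of .93 (*d* = .30) or higher", so the figure reproduces. It contains no state, pairing or baseline term, so the omission does not make it wrong.

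**2. Ignoring the matching.** Let R² be the share of between-site variance explained by the matching after the planned covariates. The article gives no value, so R² is an assumption. The reported standard error is too large by 1/√(1 − R²), and the actual two-sided type I error is about 2·[1 − Φ(1.96/√(1 − R²))]. The approximation was checked by simulating site-level means in 35 pairs (40,000 runs), analysed without the pairing:

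| R² | SE factor | Type I, formula | Type I, simulated | Coverage of 95% CI |
|---|---|---|---|---|
| 0 | 1.00 | 0.050 | 0.050 | 0.950 |
| 0.10 | 1.05 | 0.039 | 0.040 | 0.960 |
| 0.30 | 1.20 | 0.019 | 0.020 | 0.980 |
| 0.50 | 1.41 | 0.006 | 0.007 | 0.993 |

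A second simulation with 32 pairs and two 2:1 sets (32 × 2 + 2 × 3 = 70 sites; 20,000 runs) gave 0.051, 0.042, 0.020 and 0.008.

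Power in the 35-pair simulation, at an illustrative true difference of 0.7 site-level SD:

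| R² | Matching ignored | Matching respected |
|---|---|---|
| 0 | 0.82 | 0.81 |
| 0.10 | 0.84 | 0.85 |
| 0.30 | 0.86 | 0.92 |
| 0.50 | 0.90 | 0.98 |

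**3. Pre-start count.** If baseline correlates r with follow-up (assumed), adjustment multiplies the standard error by √(1 − r²): √0.75 = 0.87 at r = 0.5, and √0.51 = 0.71 at r = 0.7.

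**4. Which analyses are affected.**
- *Cross-sectional models:* each site gives one value per month, so a random organization effect recovers nothing and the loss applies in full.
- *Growth curves:* write the covariance of a site's series as R + τ·11′, with R the AR or Toeplitz error and τ the intercept variance. With complete data and an intercept and slope per arm, the covariance of the estimates is (X′R⁻¹X)⁻¹ plus τ in the intercept cell only, divided by the sites per arm. The slope variance does not contain τ.
- *Numerical check:* 34 months, 28 sites per arm, AR(1) with correlation 0.7 and error variance 1 (assumed). Reducing τ from 10 to 7 to 5 leaves the PRB-by-time standard error at 0.00918 each time. The standard error of the arm effect at time 0 falls from 0.865 to 0.730 to 0.625.

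**The case against.** The strongest reply is that this is a condensed article. Its covariate list is introduced with the word including, nothing rules out stratum or baseline terms, and such lists are often completed in an analysis plan. That carries limited weight. The open wording covers organizational characteristics taken from one cited study, and the section is otherwise specific enough to name an error structure. A model that states its terms, and gives efficiency as the reason for them, should include the factors that restricted the allocation.

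Other parts of the reply stand:
- A reader who stops at the first sentence of the model might infer that it contains only arm, time and a random organization effect. It does not: three organizational covariates follow, and the growth curves add more terms.
- The variance shares and correlations are not in the article. The relevant share is what remains after facility type, services and size, and it could be near zero.
- The loss does not carry over to the PRB-by-time slope, where each site serves as its own reference, unless the omitted factors also predict slopes.
- The Timeline lists baseline slots and naltrexone capacity. It lists no pre-start count of naltrexone administrations, so a baseline value of every outcome is not assured.
- The 2:1 sets add little. They involve six sites, and no resulting bias has been shown. Two such sets with an even split in Florida would give 36 and 34 sites, whereas the article reports 35 and 35, so even their number is uncertain.

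**Conclusion.** The point holds as one of efficiency and of consistency between design and analysis. For the month-by-month comparisons and the arm main effect, the stated models ignore the restriction on the randomization and an available baseline value. The loss from ignoring the matching runs from nothing, if matching explains no residual between-site variance, to an actual type I error of about 0.02 at 30% and 0.007 at 50%. In the illustrative case, power falls by about 6 points at 30% (0.92 to 0.86) and 8 points at 50% (0.98 to 0.90). Leaving out the baseline count forgoes a reduction in the standard error of about 13% at r = 0.5 or 29% at r = 0.7. All of these shares and correlations are assumed.

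Two stronger readings are not supported. One is that the analysis is invalid: the error is in the conservative direction, with no bias and no inflation of type I error. The other is that the stated power of 0.93 is wrong: it reproduces, and it never relied on matching or baseline. Power figures with d redefined in site-level SD units are on another scale and cannot be set against 0.93.

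**What to change.** Add one sentence to Data analysis: each primary model also includes state, the baseline number of PRB practices, baseline buprenorphine prescribing status, and the site's pre-start value of the same outcome where it was collected (assigned slots, open slots, naltrexone capacity). For naltrexone administrations, use the pre-start count if one exists and otherwise baseline naltrexone capacity. For buprenorphine use, say which baseline value applies.

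Define the pre-start value as the last one before the site's own start month. Starts are staggered and the planning phase is already part of the intervention period, so a planning-phase count is not a clean baseline.

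A random matched-set effect is an acceptable alternative to the two matching factors. Either is preferable to fixed pair effects, under which a pair that loses one site contributes nothing to the arm comparison.

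The matching factors were known at randomization, and baseline slots and capacity are already scheduled for collection. The cost is a few degrees of freedom. If the matching turns out to explain nothing, even a fully paired analysis loses only about one point of power in the simulation (0.82 to 0.81).

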### Interventions

The PRB uses two approaches to implementation: the NIATx organizational change model within a multi-organizational learning collaborative in the intervention arm and online PRB resources in both study arms. The PRB includes:Candidate identification strategies for finding prescribers interested in prescribing OUD pharmacotherapies. The Ohio “To Test a Payer/Treatment Agency Intervention to Increase Use of Buprenorphine” found the following physician specialties to be more likely to become opioid pharmacotherapy prescribers: (a) addiction medicine specialists, (b) psychiatrists who are already practicing within the organization, and (c) family medicine and internists in the community. Similarly, Rosenblatt et al. [24] observed that 81.9% of physicians with a Drug Enforcement Administration (DEA) waiver to prescribe buprenorphine came from a combination of the psychiatry, primary care, and addiction medicine specialties. The bundle recommends seeking physician prescribers from these specialties and to be aware that as of 2016, advanced practice nurses and physician assistants can also now prescribe buprenorphine [25].Prescriber education forum slide deck that can be used to inform prescriber groups and stimulate interest in OUD pharmacotherapy prescribing. Potential prescribers are often unaware of the practice opportunities in addiction medicine. Once they are aware of those opportunities, they are more likely to provide care to patients with addiction disorders [26]. Education forums can describe practice opportunities in the addiction field, how physicians and other clinicians can reduce the impact of OUDs, and give medical professionals the opportunity to express their interest in becoming OUD pharmacotherapy prescribers. The slide deck is intended for use by agency staffPrescriber-friendly workflow and risk-reduction strategies that provide clinical supports to assist prescribers with managing OUD pharmacotherapy patients. Two concerns of potential prescribers are that patients on opioid treatment pharmacotherapies require added effort and that these patients present additional clinical risk [27]. LaBelle et al. [28] reported that the use of nurses to assist physicians with the provision of buprenorphine treatment has led to expanded use of this pharmacotherapy. This strategy reduces the clinical workload on prescribers and allows for the use of a risk management plan based on existing clinical guidelines that also prevents the non-medical use or diversion of buprenorphine prescriptions [29]. Education can also be provided on how buprenorphine side effects and mortality are low, and side effects are less severe than other comparable opioid treatment alternatives [3].Academic detailing to recruit OUD prescribers. Academic detailing is an evidence-based tool to influence prescriber decision making and to recruit OUD prescribers. Developed by Soumerai et al. [30], academic detailing uses persuasive communication to influence physician behavior [31, 32]. This approach applied to recruiting OUD pharmacotherapy prescribers includes the following steps: (1) conducting interviews to investigate baseline knowledge of and motivations for buprenorphine treatment, (2) defining clear educational behavioral objectives, (3) establishing credibility by citing authoritative and unbiased sources of information and presenting both sides of controversial issues, (4) stimulating active physician and clinician participation in educational interactions, (5) using concise graphic educational materials, (6) highlighting and repeating the essential messages, and (7) providing positive reinforcement during follow-up visits. Agency staff are encouraged to use academic detailing strategies as part of physician recruitment.Telemedicine to provide access to OUD pharmacotherapies. Barriers of time and distance can limit access to OUD prescribers [11]. Buprenorphine prescribing physicians are often clustered in urban centers [24]. Some behavioral health organizations have begun to use telemedicine to increase patient access to services that are not available or if more capacity is needed in a given clinic [33–35]. For buprenorphine care, a buprenorphine prescriber can use videoconferencing to treat a patient at a remote location. Resources will be available in the PRB explaining how to use telemedicine for buprenorphine care to increase access to care and patient convenience.Promoting organizational leadership and culture to support the building of OUD pharmacotherapy capacity. Leadership and culture that supports use of opioid treatment pharmacotherapies, and the recruitment of OUD pharmacotherapy prescribers facilitates provision of this evidence-based practice [36]. Specific actions leaders can take to support recruitment include providing resources for recruiting and creating an attractive environment for applicants [37]. Examples of how to apply leadership skills to promote medication-assisted treatment use will be also included in the PRB.

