**Fig. 2 Fig2:**
[figure not shown]
PRB implementation sequence (during the 24-month intervention period). *OUD* opioid use disorders, *PRB* Prescriber Recruitment Bundle, *MAT* Medication-Assisted Therapy

During the planning phase, key components of the PRB implementation process (designed based on the evidence-based NIATx organizational change model [38, 39] include (1) defining the aim through a briefing between the executive sponsor and a project coach provided by the research team, (2) assessing PRB baseline to measure level of use of the different PRB practices and document the existing buprenorphine slots availability and extended-release naltrexone capacity, and (3) training leadership and prescriber recruiters to develop and implement an organizational change or a new practice from the bundle. The training will include all organizations within the state that were randomized to the intervention arm to encourage cross-organizational sharing. After the planning phase, a 20-month rollout phase occurs that includes (4) monitoring progress in increasing the number of buprenorphine slots, extended-release naltrexone capacity, and use of the PRB; (5) pilot testing of changes to implement and enhance PRB implementation using the evidence-based Plan-Do-Check (or measure)-Act approach [40]; and (6) sustaining successful changes by implementing a plan to institutionalize gains and avoid reverting to the old system.

Throughout the planning and rollout phases, each organization will have a coach. The coach is an expert in prescriber recruitment, OUD treatment, and organizational change who supports treatment organizations as they make, sustain, and spread PRB practices. Coaches help organizations think through key issues, offer process improvement training, and suggest changes during monthly coaching calls and e-mails as needed.

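### Grouping by state collaborative and coach exists in the intervention arm only and has no term in the primary model, so the PRB standard error may be wrong for inference beyond the three collaboratives, in a direction the protocol does not settle

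*Protocol article*

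**What the plan says.** **The model.** The Data analysis section states that "mixed-effects models (random effects due to organization and fixed effects due to study arm and time) will be used for data analysis" and that "The organizational site is the unit of analysis". The covariates are organizational characteristics, "including facility type, services offered, and organizational size, will be included in the models as covariates". For the repeated monthly counts, "we will allow errors to be auto-correlated or Toeplitz structured, denoted as AR(p) or TOEP(p), in the growth curve models". That structure describes correlation over time within one organization and none between organizations. The same section describes a design in which "treatment arms are allocated following a multi-site cluster randomization procedure", but no site-grouping factor appears among the model terms.

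**The design.** The Interventions section describes "the NIATx organizational change model within a multi-organizational learning collaborative in the intervention arm". On training, the text after Fig. 2 says: "The training will include all organizations within the state that were randomized to the intervention arm to encourage cross-organizational sharing". On coaching: "Throughout the planning and rollout phases, each organization will have a coach". It does not give the number of coaches or say whether one coach serves several sites. Under Trial design, controls receive only online access to the materials.

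**Randomization and reach.** Sites are randomized in matched pairs within state. Matching is on the number of PRB practices in use and on current buprenorphine prescribing. The Discussion says that a successful PRB could serve as a recruiting tool in underserved and other shortage areas.

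**The concern.** This is a partially nested design. Intervention sites are brought together after randomization so that they learn from each other, and control sites are not. A model whose only random effect is organization takes every site to be independent in both arms. If one state's collaborative works better than another's, the outcomes of its sites move together, and the intervention-arm mean is less precise than the model reports.

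What is at stake is the width of the confidence interval for the PRB effect and the scope of the conclusion. One unusually strong or weak collaborative could be read as a property of the PRB wherever it is used. A main effect for state does not absorb this, because the shared component sits in one arm only.

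**Working it through.** **1. The plan's own figure.** Inputs from the Sample size section: J = 56 organizations (28 per arm), n = 150 slots each, ICC ρ = 0.10, d = 0.30, alpha 0.05.

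λ = J d² / {4[ρ + (1 − ρ)/n]} = 56 × 0.09 / (4 × 0.106) = 5.04 / 0.424 = 11.89.

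Power is 0.932 by the normal approximation, Φ(√11.89 − 1.96), and 0.923 by the noncentral F on 1 and 54 df. The stated 0.93 reproduces, with the 56 organizations taken as independent. The 0.10 is a correlation of slots within a site. It says nothing about correlation between sites in one collaborative.

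**2. Intervention-only grouping.** Take 35 v 35 sites and site-level variance 1 in each arm. Let the intervention sites fall in three state groups, m = 35/3 = 11.67, with an **assumed** between-site correlation c. The ratio of the true variance of the arm difference to the model's variance is

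R = {[1 + (m − 1)c] + 1}/2 = 1 + 5.33c,

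and the true two-sided error is 2[1 − Φ(1.96/√R)].

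| c | R | error, formula | error, simulation |
|---|---|---|---|
| 0 | 1.00 | 0.050 | 0.051 |
| 0.02 | 1.11 | 0.062 | 0.061–0.064 |
| 0.05 | 1.27 | 0.082 | 0.080–0.084 |
| 0.10 | 1.53 | 0.113 | 0.115–0.116 |

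With smaller groups the inflation is less. For an assumed six coaches the formula gives 0.064 at c = 0.05 and 0.079 at 0.10; for nine coaches, 0.058 and 0.067.

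On the plan's 28 v 28 sites and d = 0.30, power with the corrected standard error (three groups, normal critical value) is 0.88 at c = 0.05 and 0.83 at c = 0.10, against 0.93.

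**3. The opposing omission.** State and pair effects are shared by both arms, so they cancel from the arm difference. A model without them still counts them as noise. Let s and p be their **assumed** shares of site variance. Taking the model's variance as the full site variance, approximately

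R = (1 − s − p) + 5.33c.

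At c = 0.05, p = 0.20, s = 0.10: R = 0.70 + 0.267 = 0.967, and the error is 0.046. Simulation gives 0.049 to 0.053. Further simulated values:
- c = 0, p = 0.20, s = 0: 0.028
- c = 0.02, p = 0, s = 0.20: 0.050
- c = 0.05, p = 0, s = 0.10: 0.074
- c = 0.10, p = 0.20, s = 0.10: 0.079

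By the formula the two omissions balance when 5.33c = s + p; with s + p = 0.30, c = 0.30/5.33 = 0.056. The document gives none of c, s or p.

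**4. What happens when the randomization factors are added.** The offset disappears and any collaborative correlation shows in full: R = 1 + 5.33c/(1 − s − p). At c = 0.05, p = 0.20, s = 0.10, R = 1 + 0.267/0.70 = 1.38, and the error is 2[1 − Φ(1.96/1.175)] = 0.095. In simulation with s = 0.10, p = 0 and c = 0.05, adding state as a main effect moves the error from 0.074 to 0.085.

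**5. Arm-by-state terms.** Testing the average of three state-specific effects against site-level error still rejects at 0.080–0.086 for c = 0.05 and 0.120 for c = 0.10 (s = p = 0). These terms display heterogeneity. They do not repair inference to other collaboratives.

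**The case against.** The strongest reply is that the collaborative is part of the treatment. The stated objective is to test the PRB together with the NIATx organizational change model, so training, sharing and coaching are components under test. If they do nothing at any site, no shared effect arises. The error exists only if the three collaboratives stand in for others. This stands: for a conclusion about these three collaboratives, the planned test does not have this error. The Discussion looks further, but as a conditional remark on potential use, not as a formal inference target.

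Three stronger readings are tempting, and the document supports none of them.

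- *That coaches are shared.* The text says only that each organization has one. Sharing is plausible but not stated, and the six- and nine-coach results are scenarios.
- *That the standard error is too small.* No collaborative or coach correlation is given. At zero there is no inflation, and leaving out state and pair can cancel or reverse a small one.
- *That the ICC of 0.10 in the Sample size section supports the 0.10 row of the table.* It belongs to a different level.

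It may also be said that such detail belongs in an analysis plan. That does not dispose of the point, because the article states the model's random effects, covariates and error structure explicitly.

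**Conclusion.** The mismatch is clear from the text: grouping is built into one arm, and the stated primary model has no term for it. Its consequence is conditional. With three state groups and no state or pair variance, type I error is about 0.06, 0.08 and 0.115 at assumed correlations of 0.02, 0.05 and 0.10, for inference beyond these collaboratives. With pair and state shares of 0.20 and 0.10 and a collaborative share of 0.05, it returns to about 0.05. Every one of these shares is an assumption, so the net direction cannot be read from the protocol. Nor should the cancellation be relied on: it is one misspecification offsetting another, and it disappears once the randomization factors enter the model. The state-wide training carries the point without any assumption about shared coaches.

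**What to change.** In the Data analysis section:

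1. Include state and the matching factors used in randomization.
2. Add arm-by-state terms, and report the three state-specific PRB effects with their average.
3. State that the inference is conditional on the collaboratives and coaches used in this trial. This sentence is essential, because items 1 and 2 alone leave the error for wider inference in place.
4. Record which coach serves which site. If coaches serve several sites and are numerous enough (for example six or more), add a coach random effect for intervention sites only, with control sites as singletons and Satterthwaite or Kenward-Roger degrees of freedom.

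A random effect over only three collaboratives is not recommended as the default. In simulation of a true difference of 0.7 site-level SD, power was 0.82 with grouping ignored and 0.57–0.69 when tested over three groups (correlation 0.05 and 0). That test still rejected at 0.06–0.07 under the null. The corresponding power was 0.73–0.79 with six coaches and 0.78–0.80 with nine.

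The cost is analysis wording and a coach identifier that the study team should already hold; no new sites or outcome data are needed. Arm-by-state terms use two degrees of freedom per outcome, and state and the matching factors use a few more. The interval may be somewhat wider and the claim is narrower.
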